
### Data management, storage and security

The COMBAT study will generate demographic, clinical, laboratory, longitudinal outcome, and multi-omic data, including transcriptomic, proteomic, metabolomic, and glycomic datasets. These data will be integrated to support biomarker discovery, disease severity stratification, and development of AI-based predictive models.

Clinical data will be entered into a secure web-based database accessible only to authorized study personnel with two-factor authentication. All participant data will be pseudonymized before entry, and no directly identifiable personal information will be stored in the central study database. Data collected across participating centres will be harmonized and curated to support quality control and downstream analyses.

Data management procedures follow the consortium Data Management Plan and adhere to the FAIR (Findable, Accessible, Interoperable and Reusable) principles. Sensitive data will be stored on secure institutional servers at Karolinska Institutet (KI) and analysed within the National Academic Infrastructure for Supercomputing in Sweden (NAISS) (https://www.naiss.se/) using the Bianca (https://www.naiss.se/resource/bianca/) secure computing environment designed for research involving sensitive personal data. Access to study data will be limited to authorized personnel according to predefined roles and responsibilities. All the data generated in Europe will be stored in compliance with General Data Protection Regulation (GDPR) and local regulations. Indian data will be stored at Indian Biological Data Centre (IBDC), Faridabad, India.

Data sharing between consortium partners will occur through secure encrypted transfer methods and controlled-access platforms. Appropriate technical and organisational safeguards will be implemented to ensure data confidentiality, integrity, and availability throughout the study. Data processing will comply with applicable ethical, legal, and regulatory requirements, including the GDPR where applicable and relevant local regulations.

Following publication of the primary study results, appropriate de-identified datasets will be deposited in recognized public repositories, including the National Center for Biotechnology Information (NCBI)/Sequence Read Archive (SRA) for genomics and transcriptomics data. The mass spectrometry proteomic data will be deposited to the ProteomeXchange Consortium (http://proteomecentral.proteomexchange.org) via the PRIDE partner repository. All the codes will be available at GitHub. Overall study design is presented in Fig. 2.

**Fig. 2 Fig2:**
[figure not shown]
Overall study design

### Study status

Prospective recruitment and sampling commenced in January 2025 and is ongoing at all participating sites. As of June 2026, 170 participants had been enrolled across the four study groups (DwoWS, DWS, SD and healthy controls) in the Guatemala (discovery) cohort; recruitment of the India (validation) cohort is initiated in July 2026 following the funding body approval. Recruitment is anticipated to be completed by November 2027, or earlier should the target sample size (100 participants per group in the discovery cohort and 150 per group in the validation cohort) be reached sooner. Because dengue transmission is cyclical and epidemic-dependent, recruitment timelines are contingent on local outbreak dynamics; should enrolment at any site fall behind target, pre-specified additional cohorts and biobanked samples will be accessed as a mitigation strategy, subject to approval by the COMBAT General Assembly.

### Study endpoint

#### Primary endpoints

Multi-omic (transcriptomic, proteomic, metabolomic and glycomic) signatures that differ significantly across dengue severity categories.A validated multi-omics-derived host biomarker panel that predicts progression to severe dengue.

#### Secondary endpoints

Dysregulated immune and metabolic pathways associated with disease severity, identified through integrative multi-omic analysis.Reproducibility of candidate biomarkers and pathways in the independent India (validation) cohort and additional external cohorts.Discrimination and calibration performance of machine-learning models integrating clinical, laboratory, demographic, virological and multi-omics features for severity prediction.Analytical and clinical performance of the focused 5–10 biomarker Olink^®^ Flex dengue severity panel.Associations between DENV serotype, host immunometabolic profile and disease severity.

## Discussion

The COMBAT study represents one of the first large-scale, multicenter efforts designed to generate systems-level insights into host responses associated with dengue severity across diverse endemic regions. By integrating multi-omics analyses within both discovery and validation cohorts, the study aims to identify molecular signatures that could facilitate earlier recognition of patients at risk of severe disease and support improved clinical and public health decision-making. The COMBAT clinical protocol framework provides the development of mechanism-based, time-aware severity prognostic biomarkers prediction with an aim to predict the severe dengue with a consensus biomarker panel [17].

Recent epidemiological data in Guatemala illustrate the dynamic and cyclical nature of dengue transmission, as well as the inherent challenges of conducting research in endemic settings [18]. Although cumulative dengue cases in 2025 were substantially lower than during the epidemic year 2024, this decline reflects a post-epidemic phase rather than elimination of transmission. Several regions remained under alert or outbreak status, highlighting persistent vulnerability to localized resurgence. Concurrent shifts in circulating serotypes and seasonal transmission patterns further complicate the epidemiological landscape, potentially altering population immunity and influencing the risk of secondary infections and severe outcomes. These fluctuations emphasize the importance of examining host biological responses under varying transmission conditions.

Acute viral infections with pandemic potential continue to reveal critical gaps in global preparedness [17]. Their clinical outcomes vary widely, from asymptomatic infection to severe or fatal disease, creating an urgent need for biomarkers that can support early diagnosis, risk stratification, and timely intervention. Although pathogen-based tests confirm infection [19], they provide limited information on disease trajectory. Widely used prognostic markers, including IL-6, CRP, and D-dimer, provide valuable information on systemic inflammation and tissue damage but have limited disease specificity across different clinical conditions, viral etiologies, disease stages, and patient populations [20–22].

Multi-omics approaches, including proteomics, metabolomics, transcriptomics, and immune profiling, have expanded biomarker discovery by capturing integrated signatures of immune activation, metabolic rewiring, endothelial injury, and organ dysfunction [23]. In chronic and noncommunicable diseases, large-scale plasma proteomic studies have successfully identified both shared and disease-specific molecular signatures with predictive value. However, applying similar frameworks to acute viral infections is more complex because host molecular profiles change rapidly with viral kinetics, symptom onset, immune activation, treatment, and recovery. Longitudinal COVID-19 and dengue studies, show that disease severity is associated not only with specific molecular markers but also with their temporal trajectories, highlighting the importance of sampling time and disease phase [24, 25].

In dengue virus (DENV) infection, multi-omics approaches have substantially advanced our understanding of the molecular signatures linked to severe clinical outcomes, including plasma leakage, hemorrhage, and shock [26]. Transcriptomic and proteomic studies have identified early dysregulation of interferon signalling, complement activation, and platelet degranulation pathways as markers of disease severity [27–29]. In parallel, metabolomic and lipidomic analyses have revealed alterations in metabolic processes, e.g., in phospholipid metabolism, arachidonic acid signalling, and amino acid utilization, reflecting immune activation, vascular dysfunction, and endothelial injury [30, 31]. Integrative multi-omics studies further suggest that metabolic and proteomic changes may emerge before overt clinical deterioration, supporting their potential as early prognostic indicators. However, variability in sampling time, host genetic background, immune history, and co-circulating DENV serotypes continues to limit cross-study reproducibility. These challenges highlight the need for temporally harmonized, geographically stratified, and serotype-aware cohorts to enable robust biomarker validation.

Several limitations warrant consideration. As an observational study, COMBAT cannot establish causal relationships between identified molecular signatures and clinical outcomes. Differences in timing of sample collection relative to symptom onset may influence observed molecular profiles. In addition, variability in transmission patterns and diagnostic capacity across sites may affect recruitment rates and cohort composition. Although laboratory-based inclusion criteria strengthen internal validity, they may reduce the ability to capture the full clinical spectrum of dengue-like illness during low-transmission periods. Achieving an appropriate balance between methodological rigor and epidemiological representativeness remains a central challenge in cohort-based infectious disease research. Finally, although we aim to develop a unified biomarker panel applicable across both settings, differences in host genetic background, environmental exposures, and other population-specific factors may limit the identification of a fully overlapping biomarker signature. In such cases, we will develop and validate region-specific biomarker panels while also identifying conserved biological pathways that may support broader cross-population applicability.

Despite these limitations, the study has notable strengths. Its prospective, multicenter design across geographically distinct endemic regions with harmonized sample collection and protocols enables evaluation of host responses under diverse epidemiological conditions. The inclusion of both discovery and validation cohorts enhances the robustness and generalizability of findings. Moreover, the multi-omics systems biology framework provides a comprehensive platform for characterizing immune and metabolic pathways associated with disease progression. Mechanism-based biomarker discovery offers a major advantage over traditional biomarker discovery in viral diseases because it identifies markers that are directly linked to the biological processes driving disease progression [24]. Rather than relying only on statistical associations between individual markers and clinical outcomes, mechanism-based approaches integrate transcriptomic, proteomic, metabolomic, immunological, and clinical data to define the pathways underlying viral replication, immune activation, endothelial injury, metabolic dysregulation, and organ damage. This improves biological interpretability and increases the likelihood that biomarkers are reproducible across cohorts, disease stages, and populations [17].

The operational challenges encountered during implementation reflect broader weaknesses in dengue surveillance and outbreak preparedness. Dependence on clinical diagnosis, under-detection of mild cases within hospital-based systems and shifting transmission patterns contribute to uncertainty in disease burden estimates and complicate early identification of patients at risk of deterioration. By identifying host biomarkers and dysregulated pathways linked to severe outcomes, the COMBAT study seeks to advance earlier risk stratification and more informed triage decisions. Such predictive tools could support more efficient allocation of healthcare resources during outbreaks and help reduce dengue-related morbidity and mortality. Beyond its immediate relevance to dengue, the integrated clinical, laboratory, and systems biology framework developed in COMBAT offers a model for strengthening preparedness against other emerging viral infections with heterogeneous clinical manifestations. In doing so, the study advances not only dengue research but also epidemic resilience and translational public health research capacity in endemic regions.

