### Statistical analysis

Differential expression analyses will be conducted separately for transcriptomic, proteomic, metabolomic and glycomic datasets with correction for multiple hypothesis testing. Integrated pathway and network analyses will be used to identify dysregulated biological processes associated with disease severity. Validation analyses will be performed using independent cohorts. As there are no high-dimensional studies with such large proteomics (> 1000 proteins) and metabolomics (> 1000 metabolites) in dengue, we have used the RNASeqSampleSize [16] to calculate the sample size for the RNA sequencing based on prior data for other viruses. Prior data indicates that the minimum average read counts among the prognostic genes in the control group is 5, the maximum dispersion is 0.5 and the ratio of the geometric mean of normalization factors is 1. If the total number of genes for testing is 20,000, the top 100 genes are prognostic and the desired minimum fold change is 2, then we will need to study 67 subjects in each group to reject the null hypothesis that the population means of the two groups are equal with probability (power) 0.8 using the Fisher’s exact test. The FDR associated with this test of this null hypothesis is 0.01. Assuming the 30% loss of samples due to the quality, we will keep 100 samples in each group for the discovery cohorts and 150 samples in each group for the validation cohorts. Beyond the RNA-seq–based calculation, the retained cohort sizes (100 per group in the discovery cohort and 150 per group in the validation cohort, after an assumed 30% attrition for sample quality) are adequate for the proteomic, metabolomic, glycomic and machine-learning analyses. The RNASeqSampleSize estimate is conservative, as RNA-seq interrogates by far the largest feature space (~ 20,000 genes) and carries greater technical dispersion than targeted proteomic and metabolomic platforms. The Olink^®^ Reveal assay measures 1,034 proteins with high reproducibility, and the LC-MS/MS metabolomic platform quantifies ~ 1,200 features, an order of magnitude fewer tests than RNA-seq. The N-glycomic analysis similarly involves a considerably smaller number of quantified glycan features. Because these targeted platforms interrogate substantially fewer analytes with lower technical variability, the sample size derived for RNA-seq represents a conservative bound expected to provide comparable or greater statistical resolution for the proteomic, metabolomic and glycomic comparisons. For the machine-learning analyses, robustness is ensured primarily through dimensionality reduction and feature selection prior to model training, together with the prospective discovery-and-validation design and external cross-site validation.

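### The condition for building region-specific panels is the lack of full signature overlap, which does not measure a between-country difference and, if signatures are selected in each country, will probably fail by chance

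*Protocol article*

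**What the plan says.** The Discussion of the protocol article states the aim of one panel for both settings. It then says that host genetics, environment and other "population-specific factors may limit the identification of a fully overlapping biomarker signature. In such cases, we will develop and validate region-specific biomarker panels". The condition is incomplete overlap, the action is to build regional panels, and the only causes named are features of the populations. Sampling error is not mentioned.

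Elsewhere:
- Study cohorts makes Guatemala the discovery cohort and India the validation cohort.
- Development of dengue severity Flex panel derives one panel of 5–10 proteins from 1,034 and takes it to both cohorts.
- The section on AI models plans external and leave-one-site-out validation with AUROC and calibration.
- Secondary endpoints lists "Reproducibility of candidate biomarkers and pathways in the independent India (validation) cohort and additional external cohorts".

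None of these is tied to the decision to build regional panels, and none compares a marker's effect between the countries.

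Statistical analysis gives the planning figures: "then we will need to study 67 subjects in each group to reject the null hypothesis" "with probability (power) 0.8", with 30% sample loss and targets of 100 and 150 per group.

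**The concern.** A marker can have the same effect in both countries, be selected in one cohort and miss the threshold or the ranking in the other. If that mismatch is put down to the population, a failure to detect is read as a difference. Selection is noisy, so some mismatch is expected even when the biology is identical.

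Two things are at stake. The study could report regional biology that is not there, and put effort into two panels, each built on one country's data, where one shared panel would have served. And a panel for India has to be developed on Indian data, so a chance mismatch would use up the study's main independent validation cohort.

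**Working it through.** **Inputs (Statistical analysis).** "If the total number of genes for testing is 20,000"; "the top 100 genes are prognostic and the desired minimum fold change is 2"; "the minimum average read counts among the prognostic genes in the control group is 5"; maximum dispersion 0.5; normalization ratio 1; power 0.8. "The FDR associated with this test of this null hypothesis is 0.01".

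**Assumptions (not in the document).** Identical effects in both countries; independent genes; all 100 prognostic genes at the planning effect.

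**1. The plan's own figure.** Per-gene significance level for FDR 0.01: (0.8 × 100 × 0.01) / (19,900 × 0.99) = 4.06e-5. An exact conditional negative-binomial test (mean 5 against 10, dispersion 0.5) has power 0.793 at 66 per group and 0.804 at 67. The stated 67 is reproduced. With 30% loss, 67 / 0.70 = 95.7, so 96, which the 100 covers.

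**2. Usable samples.** If 100 and 150 are numbers before loss, 70 and 105 remain. The same section also describes 100 and 150 as what is retained after attrition, so both cases are shown. Per-gene power p at the level in step 1:

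| | Guatemala p1 | India p2 |
|---|---|---|
| 70 / 105 | 0.833 | 0.983 |
| 100 / 150 | 0.976 | 0.9996 |

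**3. Reading A: a list is identified in each country and the two must be identical.** P = [p1·p2 + (1−p1)(1−p2)]^100.
- 70/105: (0.8189 + 0.0028)^100 = 0.8217^100, about 3e-9.
- 100/150: 0.9756^100, about 0.08.

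Chance mismatch is therefore about 92% or more. At 70/105 the expected proportion of shared genes (intersection over union) is still 0.82, so complete overlap fails although most of the list agrees.

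**4. Reading B: every Guatemala gene must be found again in India.** P(at least one fails) = 1 − [1 − p1(1−p2)]^100.
- 70/105: 1 − (1 − 0.833 × 0.017)^100 = 0.76. Unrounded powers give 0.75; powers rounded to 0.83 and 0.98 give 0.81.
- 100/150: 1 − (1 − 0.976 × 0.0004)^100 = 0.04.

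**5. Reading C: one fixed 10-marker panel is retested in India, each marker at the planning effect.** P(at least one fails) = 1 − p2^10.
- 105 per group, genome-wide level: 1 − 0.983^10 = 0.16 (0.155 unrounded). For 5 markers it is 0.08.
- 150 per group, same level: 1 − 0.9996^10 = 0.004.
- 105 per group, Bonferroni over 10 markers (0.005 each): power per marker 0.9997, so 1 − 0.9997^10 = 0.003.

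Applying the gene planning effect to protein markers is a further assumption; smaller effects would raise these figures.

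**6. Panels picked separately in each country.** Simulation took the top 5 or 10 of 1,034 independent proteins with identical true effects (4,000 runs per setting, assumed effect sizes). Full overlap occurred in 0–1% of runs when more markers of equal strength existed than places, in about 0.5–50% when strengths varied, and in 34–99.6% when exactly 10 true markers competed for 10 places.

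**7. What a direct test could detect.** The variance of a log fold change is (1/5 + 0.5 + 1/10 + 0.5)/n = 1.3/n. The standard error of the between-country difference at 70/105 is √(1.3/70 + 1.3/105) = 0.176. At 80% power, the detectable ratio of fold changes is exp[(1.96 + 0.84) × 0.176] = 1.64 for one marker at two-sided 5%, and exp[(2.81 + 0.84) × 0.176] = 1.90 with Bonferroni over 10.

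**The case against.** The sentence is a contingency in a limitations paragraph, not a formal decision rule. It can be read as applying only where a population difference has actually been found, with the method for establishing that left to a full protocol or SAP that is not shown. The described route is one panel derived from the discovery work and then validated in both cohorts, which is close to reading C, where chance failure is small. The planning inputs are also floors (lowest read count, highest dispersion, smallest fold change), so typical genes would replicate better than readings A and B suggest.

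Much of this stands. A reader might infer that a false trigger is near-certain. The documents do not support that in general: it holds for separately identified lists at 70/105 usable samples, but not for a fixed panel, and the simulated panels depend on effect sizes the article does not give. A reader might also infer that the unified panel is abandoned or would almost always be lost. The text says only that regional panels will be developed, alongside work on conserved pathways.

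What does not stand is that nothing has been fixed. The article names a condition and an action, and the condition it names is full overlap. Any unshown detail would still have to replace that condition, because on no reading does overlap estimate a difference between countries.

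**Conclusion.** The point holds as a weakness in a stated criterion. Absence of full overlap cannot separate regional difference from chance, and its false-trigger rate runs from under 1% to almost 100% depending on a reading the article does not settle. It is high where signatures are identified in each country and compared (about 92% or more). It is intermediate to low where Guatemala genes are to be re-found in India (about 75–81% at 70/105, about 4% at 100/150). It is small where a fixed 10-marker panel is retested (about 16% at most at the planning effect). These figures rest on identical effects, independent features and the plan's RNA-seq inputs; correlated features would change them. The criterion should be replaced while doing so is cheap; it is not a flaw that undermines the study.

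**What to change.** Replace full overlap as the condition with a direct comparison, fixed before India data are analysed. Study status dates the start of India recruitment to July 2026.

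1. Lock the Guatemala panel and its weights. Report its AUROC and calibration in India with confidence intervals, against a pre-set margin.
2. For each panel marker, test the severity-by-country interaction in the pooled data with multiplicity control.
3. Develop region-specific panels only if step 1 or step 2 shows a difference; otherwise keep the unified panel.
4. Report list overlap as description only.

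For choosing the margin: if the locked panel's AUROC in India were 0.80 (an assumption) with 105 severe and 210 non-severe patients, its standard error would be about 0.028, a 95% half-width of about 1.96 × 0.028 = 0.055.

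The cost is revised wording and a few models on data already planned. The downside is that interaction tests have less power than main-effect tests. A between-country ratio of fold changes well below about 1.9 (10 markers, Bonferroni, 70/105 usable) may go undeclared; the check on the locked panel's performance limits that risk.

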### Study setting

The study is conducted at clinical sites in two dengue-endemic regions, Guatemala (Central America) and India (Southeast Asia). Guatemala is an exemplary location for studying the DENV infection, owing to its distinctive combination of climatic diversity and endemic and dengue presence. Samples are collected from different hospitals following report of the outbreak. Under the India-EU cooperation on research & innovation (R&I) and co-funding partnership under the EU framework program on R&I “Horizon Europe”, samples are also collected from three hospitals in India, i.e., the Artemis Hospital and Max Health Care (a unit of Devki Devi Foundation) in New Delhi and Kasturba Hospital, Manipal, Karnataka (with diagnostic facility at Manipal Institute of Virology, MAHE, Manipal, Karnataka). Those are the two epicentres of the dengue endemic in India.

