### Study cohorts

Blood samples from patients are collected as per the WHO revised 2009 case classification [1] as: (1) dengue without warning signs (DwoWS), (2) dengue with warning signs (DWS) and (3) severe dengue (SD). Additionally, non-dengue samples will be collected from DENV-negative healthy controls (HCs). 100 individuals from each category will be collected in Guatemala and will serve as the discovery cohort, while 150 individuals from each category will be collected from India and serve as the validation cohort. The patient inclusion and exclusion criteria are presented in Table 1. Additional cohorts from Guatemala, Brazil and Honduras will be used for further validation of the dengue severity biomarkers. Validation of any additional cohorts requires a local ethical clearance, as well as approval from both the Swedish Ethical Review Authority and the COMBAT General Assembly.

**Table 1 Tab1:** Inclusion and Exclusion Criteria for patient enrolment

Inclusion Criteria: The criteria for enrolling the patients in the respective groups.
**Group 1**: Dengue without warning signs (DwoWS) Patients presenting with the following symptoms and confirmed positive for dengue infection following anti-dengue IgM or NS1 ELISA (Enzyme-linked Immunosorbent Assay) lab tests. Symptoms are fever along with at least two of the following: • Myalgia, arthralgia • Nausea and/or vomiting • Rashes • Leukopenia
**Group 2**: DENV with warning signs (DWS) Patients with the above symptoms and any of the following clinical signs: • Abdominal pain with tenderness • Persistent vomiting • Fluid accumulation • Mucosal bleeding • Restlessness, lethargy • Liver enlargement >2 cm • Laboratory findings: An increase in hematocrit levels and a rapid decrease in platelet count
**Group 3**: Severe dengue (SD) Patients with: • Severe plasma leakage leading to hypovolemic shock (dengue shock syndrome) and fluid accumulation with respiratory distress • Severe bleeding, such as epistaxis, and internal bleeding, evaluated by a clinician • Severe organ involvement with any of the following symptoms: - Liver AST or ALT ≥ 1000 - CNS: impaired consciousness - Heart and other organs failure
**Exclusion criteria**: Individuals with the following characteristics were not enrolled.

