#### Development of dengue severity Flex panel

As the main objective of the dengue severity panel is clinical deployment, we will develop a focused proteomics panel of 5–10 biomarkers derived from the mechanism-informed biomarker discovery that follows our integrative omics analysis of severe dengue. Discovery will be performed using the Olink^®^ Reveal platform, which profiles 1034 proteins, and the resulting candidates will be carried forward into a targeted Olink^®^ Flex assay containing the 5–10 prioritized biomarkers. The panel will be validated in both the Guatemala and India cohorts, with subsequent validation in additional independent cohorts.

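### The fallback to region-specific panels names no independent Indian cohort, and nothing keeps an India-built panel from counting as the validated panel of the second primary endpoint

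*Protocol article*

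**What the plan says.** Study cohorts fixes the roles: "100 individuals from each category will be collected in Guatemala and will serve as the discovery cohort", and "150 individuals from each category will be collected from India and serve as the validation cohort". For later work it adds: "Additional cohorts from Guatemala, Brazil and Honduras will be used for further validation of the dengue severity biomarkers". The Secondary objectives ask for validation in cohorts that are independent by geography, and the Secondary endpoints treat India as such a cohort.

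The second primary endpoint is "A validated multi-omics-derived host biomarker panel that predicts progression to severe dengue". The section on the Flex panel states: "The panel will be validated in both the Guatemala and India cohorts, with subsequent validation in additional independent cohorts".

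The limitations paragraph of the Discussion then concedes that genetic background, environment and "other population-specific factors may limit the identification of a fully overlapping biomarker signature". It continues: "In such cases, we will develop and validate region-specific biomarker panels". No Indian cohort is named there for the validation step, and the paragraph does not say how a regional panel relates to the primary endpoint.

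Study setting adds that "samples are also collected from three hospitals in India": two in New Delhi and one in Manipal.

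**The concern.** An India-specific panel has to be developed on Indian patients, and the only Indian patients the article describes are the validation cohort. Once their data select and weight the proteins, they are no longer independent for that panel, however good they were as a test of the Guatemala-derived one. Whether the signatures overlap can be known only after the Indian data have been analysed, so the fallback is chosen after the validation result can be seen.

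At stake is the meaning of the second primary endpoint. If the Guatemala-derived panel does not transfer, the honest report is that it was not validated in India. As written, the article would also allow a replacement panel built in India to be put forward as the validated one, on evidence that could not support that word.

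**Working it through.** **The plan's own figure.** The article's only sample-size calculation is 67 per group for RNA-seq. It reproduces: the per-gene significance level is 100 × 0.8 × 0.01 / (19,900 × 0.99) = 4.06 × 10⁻⁵. An exact negative-binomial test with control mean 5, dispersion 0.5 and fold change 2 then has power 0.793 at 66 and 0.804 at 67 per group. That figure is sound and does not bear on this point, which concerns the roles of the cohorts.

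**Step 1: who could validate which panel.**

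| Panel | Built on | Named independent cohort in the same region |
|---|---|---|
| Guatemala-derived, tested in India | Guatemala, 100 per category | Not needed; India is the test |
| Guatemala-specific | Guatemala, 100 per category | Further Guatemala cohort |
| India-specific | India, 150 per category | None named |

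Planned Indian dengue cases: 3 × 150 = 450, all in the designated validation cohort. Indian participants named outside it: 0. The gap is specific to India.

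**Step 2: what is at risk if the same patients build and test the panel.** Inputs from the article are 1034 candidate proteins, a panel of 5 to 10, and 150 per category in India, or 150 × 0.7 = 105 after the assumed 30% loss. Both sizes are shown because Statistical analysis describes 150 in one place as allowing for the loss and in another as what remains after it. Assumptions: proteins are independent, none carries any signal, the top 5 or 10 are chosen and weighted by standardized mean difference, and there are 300 runs per setting. The contrast is severe dengue against one other dengue group or against both. The true AUROC is 0.50 throughout.

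| Severe vs other | Mean AUROC, same patients, 5 proteins | Same patients, 10 proteins |
|---|---|---|
| 150 vs 150 | 0.717 | 0.775 |
| 105 vs 105 | 0.754 | 0.817 |
| 150 vs 300 | 0.687 | 0.743 |
| 105 vs 210 | 0.722 | 0.783 |

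With selection and weighting repeated inside a 50:50 split, or inside leave-one-of-three-sites-out, the mean AUROC in all eight settings lies between 0.497 and 0.504. The bias is large but avoidable with the patients already planned.

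**Step 3: what a centre split would leave.** Enrolment per Indian hospital is not given. If severe cases were spread evenly (an assumption), each hospital would have 150 / 3 = 50, or 105 / 3 = 35 after loss. A New Delhi versus Manipal split would then be 100 against 50, or 70 against 35. An uneven spread could leave one centre with too few.

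**The case against.** The strongest reply is that the article plans out-of-sample work. Its section on AI models lists time-split validation, external validation across sites and leave-one-site-out cross-validation, and Statistical analysis relies on external cross-site validation for the machine-learning work. Three Indian hospitals make this feasible within India. This stands in part. A reader might infer that the India panel will be tested on the patients who built it, but no section says so. Those methods are, however, written for the AI models and not tied to the regional panels. Even when applied with nested selection they give an honest internal estimate, not the geographically independent validation the objectives ask for.

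A second reply is that further Indian material may exist. The Flex panel section promises additional independent cohorts without naming countries, and Study status mentions additional cohorts and biobanked samples if enrolment lags. So one cannot say that no independent Indian cohort exists, only that none is named.

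A third is that a failed transfer has its own place in the reporting, because reproducibility in India is a secondary endpoint and the Discussion openly names non-transfer as a limitation. A reader might infer that the primary endpoint can never fail. The article does not say that a regional panel would satisfy it; it merely does nothing to exclude this. Incomplete overlap of signatures is also not the same as failure of a panel, since a shared panel could perform acceptably in India without full overlap.

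Finally, this is one sentence in the Discussion of a condensed article, and numerical triggers and cut-off locking commonly sit in the full protocol or analysis plan. Their absence is not held against it. What remains is a stated commitment to validate regional panels that the stated cohort roles do not support for India.

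**Conclusion.** The point holds in limited form. The article commits to validating region-specific panels, yet assigns its only described Indian cohort to validating the Guatemala-derived panel and names no other Indian cohort. It also leaves open that an India-built panel is counted towards the second primary endpoint after a failed transfer.

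The structural part rests on the text alone. The possible bias of about 0.19 to 0.32 in AUROC (0.69 to 0.82 against 0.50) rests on the simulation's assumptions and illustrates the hazard. It does not predict what the investigators will do. The Flex panel section adds some reason for care, since it also speaks of validation in Guatemala, where the panel is discovered, although that could mean confirming the targeted assay.

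This should be changed before the Indian data are analysed. Study status places the start of Indian recruitment in July 2026, so there is time.

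**What to change.** In Primary endpoints and in the limitations paragraph of the Discussion, state that the second primary endpoint is judged by the Guatemala-derived panel and cut-off, locked before the Indian data are analysed. State also that its result in India is reported as the validation result whatever it shows.

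Label any India-specific panel exploratory. Repeat feature selection and fitting inside held-out Indian sites, by leave-one-hospital-out or by a New Delhi versus Manipal split fixed before the Indian data are analysed, if severe cases per centre allow. Describe such a panel as internally validated only, and reserve independent validation for new Indian participants.

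The cost is wording in the protocol and analysis plan, with no new patients. The downsides are a smaller development set for any India-specific panel and a primary endpoint that can fail. A claim of independent validation for an India-specific panel would need a further Indian cohort.
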